# The caries-arresting effect of incorporating functionalized tricalcium phosphate into fluoride varnish applied following application of silver nitrate solution in preschool children: study protocol for a randomized, double-blind clinical trial

**DOI:** 10.1186/s13063-018-2741-1

**Published:** 2018-07-04

**Keywords:** Dental caries, Children, Fluoride varnish, Silver nitrate, Functionalized tricalcium phosphate

## Abstract

**Background:**

Dental caries in primary teeth is prevalent, affecting millions of children around the world. Functionalized tricalcium phosphate (fTCP) has been incorporated into sodium fluoride (NaF) varnish to enhance the remineralization process. NaF varnish with the adjunctive application of silver nitrate (AgNO_3_) solution is effective in arresting dentine caries. So far, there is no published randomized clinical trial investigating the effectiveness of the adoption of AgNO_3_ solution and NaF varnish containing fTCP in arresting dentine caries in preschool children. The objective of this study is to compare the effectiveness of a 25% AgNO_3_ solution plus a 5% NaF varnish containing fTCP and a 25% AgNO_3_ solution plus a 5% NaF varnish in arresting coronal dentine caries among preschool children when applied semi-annually over a 30-month period.

**Methods/design:**

This is a randomized, double-blind controlled trial. The null hypothesis tested is that no difference exists between the effectiveness of a 25% AgNO_3_ solution plus a 5% NaF varnish with fTCP and a 25% AgNO_3_ solution plus a 5% NaF varnish in arresting dentine caries in preschool children when applied semi-annually. According to the sample size calculation, approximately 2000 3- to 4-year-old kindergarten children will be screened, and at least 408 children with coronal dentine caries will be recruited. The children will be randomly allocated to two treatment groups via stratified randomization: group A – biannual application of a 25% AgNO_3_ solution followed by a 5% NaF varnish, and group B – biannual application of a 25% AgNO_3_ solution followed by a 5% NaF varnish with fTCP. Clinical examinations will be conducted every 6 months to assess whether the carious lesions have become arrested (primary outcome). Confounding factors, such as demographic background and oral hygiene behaviors, will be collected through a parental questionnaire.

**Discussion:**

The effectiveness of the topical application of a 25% AgNO_3_ solution followed by a 5% NaF varnish with fTCP in arresting coronal dentine caries among preschool children remains unknown. Because the proposed caries-arresting methods are simple, noninvasive and low cost, these can be widely recommended for caries control in young children.

**Trial registration:**

ClinicalTrials.gov (U.S.): NCT03423797 on 6 February 2018.

**Electronic supplementary material:**

The online version of this article (10.1186/s13063-018-2741-1) contains supplementary material, which is available to authorized users.

## Background

Dental caries in primary teeth is a common chronic disease in childhood. It has been ranked as the 12th most prevalent condition, affecting around 560 million children worldwide [1]. In Southeast Asian countries, caries prevalence in preschool children is very high (79%) [2], and around half (57%) of Hong Kong’s preschool children have dental caries [3]. These affected children may suffer from tooth pain and infection, possibly resulting in a serious systemic infection with severe complications [4, 5]. Poor dentition also affects children’s growth, development and general health [6]. Furthermore, dental caries has been reported as a common cause of school absenteeism in preschool children [7]. Unfortunately, children from families with lower household incomes who have limited access to dental care have higher caries prevalence and severity [3]. In this context, conventional restorative treatments are often costly and unaffordable for these underprivileged children. In addition, it is a challenge for young children to tolerate the lengthy and complicated procedures of restorative treatment. Therefore, a noninvasive and unsophisticated treatment is required to tackle the burden of dental caries in young children. This study will adopted a non-surgical strategy to arrest dentine caries in primary teeth of preschool children.

### Sodium fluoride (NaF) varnish with functionalized tricalcium phosphate (fTCP)

Results of systematic reviews have suggested that the progression of dental caries could be slowed down or halted without operative procedures [8]. The application of various topical fluoride agents has been reported to be effective in managing dental caries [9]. Fluoride varnish is one of the most commonly applied topical fluoride agents. It can adhere to tooth surfaces for longer times and acts as slow-releasing reservoirs of fluoride. A Cochrane review concluded that NaF varnish had a substantial caries-inhibiting effect on primary teeth with an estimated 37% of pooled caries being prevented [10]. Another review also found that 5% NaF varnish is effective in remineralizing early enamel caries [11].

To enhance the remineralization process, fTCP has been recently incorporated into NaF varnish. fTCP is a novel calcium phosphate system [12]. Calcium and phosphate ions are the primary minerals of the tooth structure. Adequate quantities of both ions must be present to promote ion deposition in a medium during the remineralization process [13]. fTCP works synergistically with fluoride and controls the delivery of calcium and phosphate ions to the tooth substrate. Several laboratory studies on fluoride containing fTCP showed promising results in improving fluoride’s activity and enhancing the remineralization of carious lesions [14–16]. Recently, a study found that silver nitrate (AgNO_3_) and NaF with fTCP reduced the damage of dentine caries by cariogenic biofilm [17]. Although laboratory studies revealed favorable results of incorporating fTCP with NaF varnish for caries management, the question remains as to whether NaF containing fTCP is clinically superior to NaF varnish alone.

Despite its caries-preventive effect, NaF varnish is ineffective at arresting coronal dentine caries [18]. Adjunctive application of AgNO_3_ solution followed by application of NaF varnish has been advocated to improve caries-arrest effectiveness.

### Adjunctive application of AgNO_3_ solution and NaF varnish

AgNO_3_ solution has been used as an antimicrobial agent for years. However, the adoption of AgNO_3_ solution diminished because of the discovery of fluoride for caries management in the mid-nineteenth century [19]. Because AgNO_3_ solution has strong antibacterial properties and NaF varnish has remineralizing properties, the application of AgNO_3_ solution followed by NaF varnish was reintroduced to manage caries in young children [20]. A retrospective study conducted in the United States reported that more than 5000 children were treated with this protocol, and the results revealed that almost all cavitated dentine lesions became arrested after treatment [20]. Subsequently, the number of young children requiring full-mouth rehabilitation under general anesthesia decreased substantially. An in vitro study also confirmed the caries-arresting effect of a 25% AgNO_3_ solution followed by a 5% NaF varnish in remineralizing artificial dentine caries and inhibiting the degradation of collagen [21]. A 12-month randomized clinical trial showed no difference between silver diamine fluoride (SDF) and 25% AgNO_3_ solution followed by a 5% NaF varnish in arresting dentine caries among preschool children [22].

So far, there is no published randomized clinical trial investigating the effectiveness of the adoption of AgNO_3_ solution and NaF varnish containing fTCP in arresting dentine caries in preschool children.

### Objective

The objective of this randomized, double-blind controlled trial is to compare the caries-arresting effectiveness of a 5% NaF varnish with fTCP and that of a 5% NaF without fTCP when applied semi-annually following the application of a 25% AgNO_3_ solution in preschool children over 30 months. The secondary objective is to compare the effectiveness of a 5% NaF varnish with fTCP and that of a 5% NaF without fTCP in preventing dental caries in preschool children over 30 months.

### Hypothesis

The null hypothesis is that there is no difference between the caries-arresting effectiveness of the semi-annual application of a 5% NaF varnish with fTCP and that of a 5% NaF without fTCP following the application of a 25% AgNO_3_ solution in preschool children over 30 months.

## Methods/design

### Trial design

This is a double-blind, two-armed, parallel-design randomized controlled trial. The Standard Protocol Items: Recommendations for Interventional Trials (SPIRIT) 2013 Statement will be followed in this trial (Additional file 1) [23]. The schedule of this study is presented in Fig. 1.

**Fig. 1 Fig1:**
[figure not shown]
Schedule of enrollment, interventions, and assessments

### Setting

Kindergartens that have joined the outreach dental service provided by Faculty of Dentistry, The University of Hong Kong, will be invited to join this study. Preschool children, who are aged 3 to 4 years, will be invited to participate in the trial. An invitation letter explaining the purposes, procedures of the study and potential adverse effects will be distributed to the parents or legal guardians of the invited children. Written parental consent will be sought prior to the oral examination and dental treatment (Additional file 2).

### Participants

The eligibility criteria for participating children are as follows: (1) be generally healthy, (2) have written parental consent and (3) have at least one cavitated dentine carious lesion. The exclusion criteria are as follows: (1) children who are uncooperative or who refuse examination and (2) children who have major systemic illnesses or are on long-term medications. A tooth with pulpal exposure or with any signs and symptoms of irreversible pulpitis or a non-vital pulp, such as tooth discoloration, will be excluded.

### Screening and recruitment

Oral examination and treatment will take place in kindergartens during school hours. An outreach dental team is comprised of dentists and research assistants. Prior to conducting the study, they will be trained by experienced specialists ([name] and [name]). A calibrated examiner will screen all children who have had parental consent given. After that, participants who meet the inclusion criteria will be recruited.

### Clinical examination

Clinical examination of the children will be performed mainly through a careful visual inspection with the aid of a World Health Organization CPI probe (405/WHO probe, Otto Leibinger, Mühlheim, Germany) and a disposable dental mirror with an attached light-emitting diode for intra-oral illumination (MirrorLite, Kudos Crown Limited, Hong Kong Special Administrative Region of the People’s Republic of China). Tooth status (decayed, missing and filled tooth surfaces (dmfs) scores), tooth mobility and tooth discoloration will be recorded. Caries will be diagnosed at the cavitation level. The visual-tactile assessment will be adopted to assess the status of carious lesions. They will be gently explored with a CPI probe in the centre of the lesion. Great care will be taken to avoid damaging the tooth. For the posterior teeth, all five surfaces (buccal, lingual, mesial, distal and occlusal) will be assessed, while four surfaces (buccal, lingual, mesial and distal) of the anterior teeth will be examined.

The oral hygiene status will be measured using the Visible Plaque Index (VPI). The buccal and lingual surfaces of six index teeth (55, 51, 63, 71, 75 and 83) will be examined. The presence or absence of visible plaque on the carious surface will also be recorded. No dental radiograph will be taken because this study will be conducted in a school-based setting.

A trained dentist will perform the examinations (baseline and follow-ups) throughout the 30-month study. The intra-examiner agreement on the plaque and caries assessment will be performed in 10% of the children at each stage of the study.

### Questionnaire survey

A parental questionnaire regarding each child’s oral hygiene, snacking habits, use of fluoride agents, dental-visit behavior, parental educational level and family monthly income will be administered at baseline and at 12-, 18- and 30-month follow-up visits. To assess the children’s oral-health-related quality of life, the translated and validated Chinese-language Early Childhood Oral Health Impact Scale (ECOHIS) will be adopted in the parental questionnaire. The questionnaires will also assess parental satisfaction with their child’s oral health and dental esthetics. In the follow-up questionnaire, parents of the study children will also be asked to report the post complications of assigned treatments, such as pain, from a treated tooth and gingival irritation around a treated tooth.

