### Interventions

A dentist who is not involved in the assessment of the carious lesions will apply the solution and varnish with a micro-brush on the carious lesion according to the assigned treatment group after the oral examination.

Two intervention groups in this study are as follows:Group A: a 25% AgNO_3_ solution (25% silver nitrate, Gordon Labs, Carson, CA, USA) followed by a 5% NaF varnish (Nupro White Varnish, Dentsply, York, PA, USA),Group B: a 25% AgNO_3_ solution (25% silver nitrate, Gordon Labs, Carson, CA, USA) followed by a 5% NaF varnish with fTCP (Clinpro White Varnish, 3 M, St. Paul, MN, USA).

After applying the solution and varnish on the carious lesion(s) for arrest purposes, the assigned 5% NaF varnish (0.25 ml) will be applied on all tooth surfaces of each child to prevent dental caries according to their assigned treatment group. After the treatment, the children will be instructed not to eat or drink for 30 min. The intervention will be provided every 6 months.

An individual report on the child’ s oral health status will be distributed to the parents or guardians with a note asking them to report to the study dentist if there are any adverse effects on the treated tooth and/or the surrounding gum and mucosa after treatment. A referral letter will be provided to seek the appropriate dental treatment if needed. Parents and teachers will be informed that if the treatment has successfully arrested the carious lesions, yellow and soft carious surfaces will become hard and black in color.

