### Follow-up evaluation

Follow-up clinical examinations will be conducted semi-annually by the same examiner in kindergartens for 30 months. The same diagnostic criteria, equipment and clinical procedures that were used in the baseline examination will be adopted in the follow-up evaluations. The caries status (dmfs index) and oral health status (VPI) of the children will be recorded. In addition, the status of the carious surfaces included in the study at baseline examination and the presence of visible plaque on those carious surfaces will be assessed. Newly developed carious lesions will be recorded and treated with the assigned treatment intervention. The examiner will also look for related side/adverse effects, including blackening of the treated carious surfaces, discolored teeth, tooth mobility and abscess formation during the follow-up oral examinations. Reasons for tooth loss prior to follow-up will be recorded.

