## Discussion

This is a randomized, double-blind clinical trial aiming to investigate the caries-arresting effectiveness of the semi-annual application of a 25% AgNO_3_ solution followed by a 5% NaF varnish with/without fTCP among preschool children. The caries-preventive effect, parental satisfaction, changes in oral-health-related quality of life of the study children and the adverse effects of the two intervention groups also will be evaluated.

Due to the limitations of the study, the use of dental radiographs is unavailable and unsafe when conducting a trial in kindergartens [18, 24]. The visual-tactile inspection without x-rays will be adopted for assessing the lesion activity at baseline and follow-up examinations, which is similarly to other caries-arresting studies [28]. To generalize the research findings to general populations, the recruited children will not be asked to change their routine oral care practices including the use of fluoride toothpaste and tooth-brushing habits. Instead, the data of oral care practice habits will be collected by questionnaires and analyzed as confounding factors. The 30-month study period is optimal to investigate the effect of caries-arresting treatment in the long run. The follow-up examinations, which will be conducted every 6 months, will provide the trends or changes of lesion activities over 30 months after receiving the intervention. After finishing this study, all recruited children will be eligible to attend primary schools, and the decayed teeth can be restored by School Dental Care Service which is provided by the Department of Health for primary school students in Hong Kong.

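### The only structured question to parents on pain and gum irritation comes 6 to 12 months after each application, so short-lived reactions are likely to be under-counted, to a similar degree, in both arms

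*Protocol article*

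**What the plan says.** The Discussion of the protocol article announces that "the adverse effects of the two intervention groups also will be evaluated". Three routes could supply the data.

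- **Parental questionnaire** (Questionnaire survey). "In the follow-up questionnaire, parents of the study children will also be asked to report the post complications of assigned treatments". Two examples of what parents may report are then listed: "such as pain, from a treated tooth and gingival irritation around a treated tooth". The questionnaire "will be administered at baseline and at 12-, 18- and 30-month follow-up visits", so there is none at 6 or 24 months.
- **Note sent home** (Interventions). The child's report comes with a written message for parents: "asking them to report to the study dentist if there are any adverse effects on the treated tooth and/or the surrounding gum and mucosa after" each application.
- **Examination** (Follow-up evaluation). "Follow-up clinical examinations will be conducted semi-annually by the same examiner in kindergartens for 30 months". At these visits, "The examiner will also look for related side/adverse effects, including blackening of the treated carious surfaces, discolored teeth, tooth mobility and abscess formation".

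On treatment, the Interventions section says: "The intervention will be provided every 6 months".

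**The concern.** Pain from a treated tooth and irritation of the surrounding gum are reactions that one would expect soon after an application and that may be gone within days. The one instrument that puts these items to every parent is spaced at 6 or 12 months from the applications it has to cover, and two of its three follow-up rounds cover two applications at once. A parent must then recall a mild event from half a year or a year before and place it after the right visit.

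What is at stake is how good the reported adverse-effect rates are, and how much a comparison of them could show. The article expects the method to be widely recommended for young children, so credible rates of short-term reactions are useful whichever varnish performs better.

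**Working it through.** **Inputs.** Treatment every 6 months (Interventions). Follow-up questionnaires at 12, 18 and 30 months (Questionnaire survey). 204 children per group at baseline (Sample size and power calculation). Assumption: treatment starts at baseline, so the applications that the 30-month visit can look back on fall at 0, 6, 12, 18 and 24 months. The schedule figure is not available to confirm this.

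**Step 1: lag from application to first structured question.** Lag = month of the next questionnaire minus month of the application, taking each form as completed before that visit's treatment.

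| Application (month) | Next questionnaire (month) | Lag (months) |
|---|---|---|
| 0 | 12 | 12 |
| 6 | 12 | 6 |
| 12 | 18 | 6 |
| 18 | 30 | 12 |
| 24 | 30 | 6 |

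No application is asked about sooner than 6 months, and 2 of 5 wait 12 months. The 12-month form covers the applications at 0 and 6 months, and the 30-month form those at 18 and 24 months.

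**Step 2: the timing assumption.** The article does not say whether parents fill in the form before or after that visit's treatment. If after, the 12- and 18-month applications could be asked about almost at once. The applications at 0, 6 and 24 months would still have lags of 12, 6 and 6 months. So between 3 and 5 of the 5 applications have a lag of at least 6 months.

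**Step 3: would questionnaires at 6 and 24 months close the gap?** With forms at 6, 12, 18, 24 and 30 months, still completed before treatment, every lag becomes 6 months. The double coverage goes, but recall is still half a year.

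**Step 4: the other two routes.** The note has no built-in delay and names the tooth and the gum. It asks for a report only if something has happened, so a silent parent may have seen nothing or may not have reported it. The examiner's list names blackening, discoloration, mobility and abscess. Even if it is not exhaustive, a reaction that has resolved cannot be seen 6 months later.

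**Step 5: illustration of the loss.** The plan's 204 per group reproduces from its own inputs: design effect 1 + (3 − 1) × 0.13 = 1.26; 410 × 1.26 / 3 = 172.2, so 173; 173 / 0.85 = 203.5, so 204. The documents give no reaction rates and no recall fraction, so all the rates below are assumed. Take true irritation rates of 10% and 5% per application, with the same fraction recalled in each arm. Power uses the arcsine approximation at two-sided 0.05: Φ(h√(204/2) − 1.96), where h = 2 arcsin√p₁ − 2 arcsin√p₂.

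| Fraction captured | Observed rates | Expected events per arm | h√102 | Power |
|---|---|---|---|---|
| 100% | 10% v 5% | 20 v 10 | 1.94 | about 49% |
| 50% | 5% v 2.5% | 10 v 5 | 1.35 | about 27% |
| 20% | 2% v 1% | 4 v 2 | 0.84 | about 13% |

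The ratio between arms stays at 2:1 throughout. The observed rates, their absolute difference and the power all fall.

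**The case against.** The strongest reply is that the questionnaire is not the only request to parents. The note in the Interventions section goes home with the child's report, names the treated tooth and the surrounding gum, and carries no delay. This stands. A reader might infer from the questionnaire schedule that parents are not otherwise asked and that the comparison will miss these reactions, but the documents do not support that. What remains is that the note is spontaneous reporting. The number of treated children is known, but not how many of their parents would have reported an event.

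A reader might also infer that a result of no difference in adverse effects would be produced by the timing alone. That too goes beyond the documents. The Blinding section says that children and parents are not told the allocation, both arms follow the same schedule, and both receive the same silver nitrate solution. Under-recall should therefore be similar in the two arms. In the illustration, even complete capture at one visit (20 of 204 v 10 of 204) gives z of about 1.9 and p of about 0.06 without continuity correction. Late recall is thus not what separates a clear difference from a null one.

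Two further points are fair. The order of questionnaire and treatment at a visit is not stated, which is why the lags above are conditional. How reports prompted by the note are logged and summarised is detail that an article may leave to the full protocol, and its absence is not criticised here. The criticism concerns the questionnaire times, the questionnaire items and the form of the note, all of which the article does state.

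**Conclusion.** The point holds as a minor one. Structured questioning on pain and gum irritation comes 12, 6, 6, 12 and 6 months after the five applications if forms precede treatment. If they follow it, three of the five still have lags of 6 to 12 months. Neither the passive note nor the examination fills that gap, so short-lived reactions are likely to be under-counted.

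The consequence is understated rates, uncertain attribution of an event to an application, and lower sensitivity of the adverse-effect comparison. The size of the loss cannot be taken from the documents; the illustration shows only its direction under assumed rates. The plan gives no ground for expecting bias towards one varnish. The Outcome measure section names lesion arrest as primary and caries increment as secondary, so neither of these, nor the sample size, is affected.

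The conclusion rests on three assumptions: applications at 0, 6, 12, 18 and 24 months, reactions that mostly resolve well before the next visit, and similar recall in the two arms.

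**What to change.** For the applications still to come (recruitment began in September 2017, so some have already passed), turn the existing note into a short return slip. It would have yes/no boxes for pain, gum irritation and other problems in the first days after treatment, and would be returned through the kindergarten for every treated child whether or not anything happened. Report the resulting rates by arm and by application, with the return rate for each, as the main parent-reported adverse-effect data. Keep the 12-, 18- and 30-month questionnaire items as supporting data. Adding questionnaires at 6 and 24 months would not be enough, because the lag would still be 6 months.

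The cost is one reprinted slip per application and entry of a few yes/no fields, with no extra visit, staff or procedure. The downside is that some slips will not come back, so the rates will rest on those returned.
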